### Adverse events

During the trial, participants will be asked about adverse events. All adverse events will be reported and followed up until solved or as required. The type and duration will be recorded.

Participants will be asked to contact the trial investigator or hand surgeon whenever they wish to discuss or report any events during the trial. Concomitant cares are not permitted.

### Follow-up and outcomes measures

Patients will complete a baseline questionnaire, which includes clinical, sociodemographic data, and potential prognostic factors.

The primary outcome measure will be the visual analog scale (VAS) determined by changes in the distance between the patient-made marks. VAS is reliable, valid, and responsive in detecting improvements associated with pain treatment [33].

Secondary outcome measures include the Quick Disabilities of Arm, Shoulder, and Hand (QUICK DASH), a short, reliable, and valid measure of physical function and symptoms related to upper-limb musculoskeletal disorders [34, 35]. Patient-Rated Wrist Evaluation (PRWE) is a widely used measure of patient-reported disability and pain related to wrist disorders [36]. The grip strength using a dynamometer [37], followed by lateral (key) and pulp-to-pulp pinch, will be recorded (both in kilograms) with a JAMAR pinch meter [38]. The goniometry measurement is determined by a change in the range of motion, as defined by the IFSSH (Atlas of Surface Anatomy and Joint Motion. International Federation of Societies for Surgery of the Hand [Internet].Illinois. Accessed 18 December 2018. < https://ifssh.info/terminology_hand_surgery.php >). The health-related quality of life questionnaire EuroQol 5-dimensions (EQ-5D-5L) is a standardized instrument for measuring generic health status [39].

Health economic outcomes include the impact of the surgery on work and other activities (including work absence and reduction in work permanence). Direct medical costs will be calculated using activity-based cost analysis. Indirect costs will be added to the direct costs, which will be calculated using the demographics variables. The remuneration (average earnings or salary) is considered a reasonable measure of labor productivity.

The main investigator will check that the questionnaires are complete. If participants choose to withdraw from the trial, they will be asked if they agree with their data being used in this study.

### Data collection method and management

Before surgery, every measure has to be collected in baseline data form. If not collected the patient could not be operated on until it is done. Then after surgery, every appointment is duplicated, with the hand surgeon and principal investigator separately. If the patient does not attend the appointment, will be called by phone with a new appointment.

Each participant will be assigned a unique identifier and a unique data case report form that includes all measures collected at the different time-points (Fig. 1) and will be used for all data documentation to assure the participant’s confidentiality. All data will be digitalized and stored in a central database. Data will be stored for at least ten years after study completion.

The senior hand surgeon will keep all records related to randomly assigned participants. The trial will be monitored regularly and the records will be examined on a monthly basis by two members (principal investigator and a statistician), to ensure that the conduct of the trial is in accordance with the trial protocol. The steering committee will comprise the principal investigator, a statistician, and a senior hand surgeon. The data management team will include the trial’s principal investigator (SL) and a statistician (AY). A follow report will be reported to the Ethics Committee every year.

The full protocol and dataset supporting the findings of the study will be available in the Docusalut repository (https://docusalut.com). Results will be presented at national and international meetings, and published in peer-reviewed orthopedics, hand surgery, and hand therapy journals.

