### Randomization and blinding

Patients will be randomized by the senior hand surgeon ([name]), via a remote web-based randomization system (OxMar Software, *Oxford Minimization and Randomization, an open source software*) [31], which ensures a concealed allocation sequence. Randomization will be stratified by sex and group age. Each participant will be assigned a unique identification number and a unique data case report form.

The participants and the senior hand surgeon will know the assigned treatment. The participants will have the appointments and controls as in our usual clinical practice.

The main investigator will be blinded to the treatment assignment and will collect the measures in the collection notebook, except for the radiological variables because of their association with the participant’s ID. The main investigator will assess the participant before the surgeon, on the same day in a different office.

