### Post-operative care

All patients will be included in a same day outpatient surgery protocol, and discharged from the hospital few hours after the surgery. The post-operative pain management is a combination of ibuprofen 600 mg/12 h, paracetamol 1 g/8 h, tramadol 50 mg/8 h and omeprazole 20 mg every 24 h, taking into account the possible adverse effects or contraindications.

All participants will be asked to attend to the first appointment with a nurse 2 days after surgery, to check the wound and to change the bandage. Patients will be asked about the tolerability of the surgery and any adverse events will be recorded. The next appointment will be about 10 days later to remove stitches, maintaining the splint until 3 weeks after the surgery.

Group A participants must wear a removable abduction splint, for 3 more weeks. The patients will be instructed on how to put and remove the abduction splint to start opposition exercises. Finally, Group A participants will start a standardized rehabilitation protocol.

Group B participants the splint will be removed 3 weeks after surgery. They will be instructed on how to do opposition and strengthening exercises at home. They will not attend to rehabilitation sessions in the hospital.

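### The investigator presented as the blinded assessor appears also to examine trial records monthly and to sit on the data management team, with no masking described

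*Protocol article*

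**What the plan says.** Four sections of the protocol article bear on this.

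- **Randomization and blinding.** "The main investigator will be blinded to the treatment assignment and will collect the measures in the collection notebook", with one exception: "except for the radiological variables because of their association with the participant’s ID". This investigator sees the patient ahead of the surgeon on the visit day, in another room. The section also states: "The participants and the senior hand surgeon will know the assigned treatment".
- **Data collection method and management.** After surgery, "every appointment is duplicated, with the hand surgeon and principal investigator separately". The section says that the senior surgeon holds the records of randomised patients. It then says that "the records will be examined on a monthly basis by two members (principal investigator and a statistician" are the two, the purpose being to verify that conduct follows the protocol. The same two roles are listed as the data management team, and both join the senior surgeon on the steering committee. The case report form carries all measures under a unique identifier, and all data go to one central database.
- **Adverse events.** "Participants will be asked to contact the trial investigator or hand surgeon whenever they wish to discuss or report any events during the trial".
- **Post-operative care.** The arms are treated differently after the first three weeks: "Group A participants must wear a removable abduction splint, for 3 more weeks". Group A then has a standard rehabilitation programme. Group B exercises at home without hospital sessions.

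**The concern.** A blinded assessor should not have duties that ordinarily show which operation a patient had. Here one role seems to hold both the assessment and the oversight of individual records.

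Grip strength, pinch strength and goniometry depend partly on how the examiner instructs, encourages and positions the patient, so an examiner who knows the arm can shift them without intending to. Mobility and pinch strength are also among the reasons the Background gives for developing the prosthesis. If the blind on these outcomes cannot be defended, a difference between arms will be hard to interpret, and the description of the trial as blinded will be open to challenge.

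**Working it through.** The point turns on roles, and the article gives no figure to reproduce. The check sets the sections side by side.

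1. **Is the blinded assessor the principal investigator?** Randomization and blinding gives the separate visit, apart from the surgeon's, to the main investigator. Data collection method and management gives the same paired visit to the principal investigator. No other assessor apart from the surgeon is described for it. The two titles therefore read as one role. This is an inference, but the natural one.

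2. **What else does that role do?** It takes part in the monthly examination of records, holds one of two listed places on the data management team, and sits on the steering committee with the unblinded surgeon.

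3. **Would the monthly examination show the arm?** Its purpose is adherence to the protocol. The protocol prescribes different operations (Operative treatment, Groups A and B), different splint durations and different rehabilitation (Post-operative care). Adherence to arm-specific procedures cannot ordinarily be checked without seeing which were delivered. The article mentions no masked extract and no restriction of access for this task.

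4. **Does the article itself treat such data as a threat?** Yes. It keeps the radiological variables from the blinded investigator because they link to the participant's ID. It then gives the same role the examination of records and a place in data management, where data are held under a unique identifier, and does not repeat the exception.

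5. **Adverse events.** The contact is the trial investigator or the surgeon, without saying which investigator is meant. The Discussion names dislocation and loosening of components as the prosthesis's most common complication. A report of either would identify the arm, so the assessor may learn it by this route.

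6. **Which outcomes are exposed?** VAS, Quick DASH, PRWE and EQ-5D-5L come from patients who know their treatment, so blinding the assessor does little for them. Grip, pinch and range of motion are taken by the examiner at every appointment.

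7. **Scale, as an upper bound on opportunity.**
   - Follow-up visits: 6 weeks and 3, 6, 12, 24, 36, 48 and 60 months = 8.
   - Patient-visits without loss: 106 × 8 = 848.
   - With the assumed 10% loss, all taken before the first visit: 106 × 0.9 = 95.4, about 95 patients, and 95 × 8 = 760.
   - Monthly examinations from February 2021 to February 2026, the expected end of recruitment: 5 × 12 = about 60, with follow-up continuing afterwards.
   - Group A's splint: 3 + 3 = 6 weeks, so it could be a cue at the 6-week visit at most, 1 of 8.

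   These figures count occasions on which the blind is unprotected. They do not measure unblinding or bias.

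**The case against.** The strongest reply is that the article does not say which records are examined or that they show the allocation. The case report form is described by its identifier and measures, with no mention of arm. Records of randomised patients stay with the surgeon, which could be meant to keep them with someone already unblinded. Care was taken elsewhere: the assessor goes first, in a different office, without the radiological variables, and both operations use the same skin incision design. A journal article may also leave access rights to the full protocol.

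Much of this stands, and it rules out several stronger readings:

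- A reader might infer that the blind cannot hold or has already failed. The documents do not show this, because masked records could be in use.
- A reader might infer that the principal investigator takes the adverse-event calls. The text names neither the main nor the principal investigator and offers the surgeon as an alternative.
- A reader might infer that the principal investigator runs data management. The text gives membership of a team.
- A reader might take the 8 visits, 106 patients and 60 examinations as the size of the bias. They are opportunities only, and the removable splint is a weak cue at a single visit.

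The reply does not remove the central conflict, which does not rest on silence about detail. The article assigns to one apparent role both a blind and a duty that ordinarily breaks it.

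**Conclusion.** The point holds as a contradiction in the assigned roles that leaves the assessor's blind unprotected. It concerns the examiner-measured secondary outcomes (grip, pinch, range of motion) at up to 8 follow-up visits. It does not touch the VAS primary outcome. The direction and amount of any bias cannot be derived from the documents.

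The conclusion rests on two assumptions: that main investigator and principal investigator are the same person, and that the monthly examination uses unmasked individual records. If either is false, stating so in the protocol would settle most of the point, leaving only the open adverse-event contact. It should be corrected, because recruitment is under way and follow-up runs for years.

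**What to change.** Reconcile the sections Randomization and blinding, Adverse events, and Data collection method and management as follows.

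- State whether the main and the principal investigator are one person.
- Assign the unmasked monthly record examination to the statistician, together with the handling of operative, radiological, rehabilitation, cost and adverse-event data.
- Limit the assessor, for as long as that person is assessing patients, to arm-masked outcome pages and group-level results. The principal investigator can then still take part in the 1-year and later analyses.
- Name a contact other than the assessor for adverse-event reports.
- Ask patients not to tell the assessor which operation they had.

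**Cost.** This means changed access rights and a standing instruction, with no new staff. The principal investigator loses routine access to arm-revealing individual records while still assessing. The statistician will know the arms, but the article claims no blind for that role, so no stated safeguard is lost. Moving the examination to the surgeon instead would be less suitable, since the surgeon randomises the patients and keeps the records to be checked.

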### Statistical analysis

#### Sample size

A total of 106 participants will be necessary (53 subjects for each treatment group) to detect differences equal to or greater than 30% in the visual analog scale (VAS) on the baseline status of the patient [33]. Accepted values will be for an alpha risk of 0.05 and a beta risk of 0.1, in a bilateral contrast. The common standard deviation is assumed to be 1.5. It is assumed that 10% of the trial patients will be lost.

#### Primary analysis at 1 year

The results will be analyzed by using Statistical Package for Social Sciences (SPSS 20.0, IBM Corp., Armonk, NY, USA) software. A descriptive analysis of the collected data will be obtained by using the mean and the standard deviation for the quantitative variables that follow a normal distribution. For those whose data do not follow normal distribution, the median and range will be calculated.

Differences shall be detected by chi-square or Fisher’s tests for categorical variables and Student’s *T* or Mann–Whitney test for the resultant variables. After randomization, a descriptive comparison will be carried out to find out similar variable distribution.

The primary analysis will be carried out by intention-to-treat (ITT). The main variable, VAS, will be used as a continuous variable to confirm the main hypothesis, and a non-parametric mean comparison analysis (Mann–Whitney *U* test) will be performed.

The clinical effectiveness analysis will follow the recommendations established by CONSORT, including its safety extension [40].

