**Methods:**

A randomized, blinded, parallel-group superiority clinical trial comparing trapeziectomy with abductor pollicis longus (APL) arthroplasty and prosthetic replacement with Maïa® prosthesis. Patients, 18 years old and older, with a clinical diagnosis of unilateral or bilateral TMC OA who fulfill the trial’s eligibility criteria will be invited to participate. The diagnosis will be made by experienced hand surgeons based on symptoms, clinical history, physical examination, and complementary imaging tests.

A total of 106 patients who provide informed consent will be randomly assigned to treatment with APL arthroplasty and prosthetic replacement with Maïa® prosthesis. The participants will complete different questionnaires including EuroQuol 5D-5L (EQ-5D-5L), the Quick DASH, and the Patient Rated Wrist Evaluation (PRWE) at baseline, at 6 weeks, and 3, 6, 12, 24, 36, 48, and 60 months after surgical treatment. The participants will undergo physical examination, range of motion assessment, and strength measure every appointment. The trial’s primary outcome variable is the change in the visual analog scale (VAS) from baseline to 12 months. A long-term follow-up analysis will be performed every year for 5 years to assess chronic changes and prosthesis survival rate. The costs will be calculated from the provider’s and society perspective using direct and indirect medical costs.

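### The primary analysis is labelled intention-to-treat, but the only method named for it, an unadjusted Mann–Whitney test on 12-month VAS, can include only patients with a 12-month value unless values are imputed

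*Protocol article*

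**What the plan says.** Four statements in the protocol article bear on this point.

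- **Endpoint** (Abstract, Methods): the "primary outcome variable is the change in the visual analog scale (VAS) from baseline to 12 months". This is one post-operative time point.
- **Principle** (Primary analysis at 1 year): "The primary analysis will be carried out by intention-to-treat (ITT").
- **Method** (same section): VAS is treated as continuous and "a non-parametric mean comparison analysis (Mann–Whitney *U* test) will be performed". No covariate, repeated-measures model or imputation is named.
- **Expected loss** (Sample size): "It is assumed that 10% of the trial patients will be lost".

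The Abstract also lists visits at 6 weeks, 3 months and 6 months before the 12-month visit. Its visit sentence names EQ-5D-5L, Quick DASH and PRWE as included questionnaires, but not VAS. The section Data collection method and management says the case report form holds all measures at the time points of Fig. 1, which is not shown. VAS at the earlier visits is therefore implied but not stated outright. Randomization is stratified by sex and age group, and baseline measures are compulsory before surgery. The named test uses neither the strata nor baseline VAS as a covariate.

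**The concern.** Intention-to-treat leads a reader to expect every randomised patient to be compared in the assigned arm. A two-sample rank test on a single visit needs one number per patient. A patient without a 12-month VAS can enter only if a value is supplied, and nothing in the stated method supplies one.

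What is at stake is bias, and the match between the label and the analysis, more than power. If patients who leave differ in pain from those who stay, and differ by unequal amounts in the two arms, the 12-month comparison is shifted and a larger sample does not remove the shift. Unequal loss is possible here. Participants know their treatment (Randomization and blinding), and only Group A enters the standardized rehabilitation protocol, while Group B has no hospital rehabilitation sessions (Post-operative care). The documents do not say that loss will differ, or in which direction.

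**Working it through.** **Inputs from the protocol article (Sample size).** "A total of 106 participants will be necessary (53 subjects for each treatment group"); two-sided alpha 0.05 with 90% power; SD 1.5 in each arm; 10% loss. The effect is given as 30% of baseline VAS with no baseline mean, so the absolute difference is not documented.

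**1. The plan's figure of 106.** It cannot be reproduced from the stated inputs alone. Assume a difference δ = 1.0 VAS point, a value found by solving backwards:

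- n per arm = 2 × SD² × (1.960 + 1.282)² / δ² = 2 × 2.25 × 10.51 / 1.0 = 47.3, rounded up to 48.
- 48 × 1.10 = 52.8, rounded up to 53 per arm, or 106 in total. This matches.
- Dividing instead, 48 / 0.90 = 53.3, rounded up to 54 per arm, or 108.

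On this reading, 106 was chosen so that the test could run on about 48 observed patients per arm.

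**2. Patients available to the named test.** 0.10 × 106 = 10.6, so about 11 patients have no 12-month value. 0.90 × 106 = 95.4, so about 95 remain, or 47 to 48 per arm (53 × 0.90 = 47.7).

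**3. Possible bias.** Let g be the difference between arms in how far lost patients' 12-month VAS departs from that of retained patients, with 10% lost in each arm. Then bias = 0.10 × g. For the false-positive rate, take a two-sided 5% t-test with 48 per arm and SD 1.5, so SE = 1.5 × √(2/48) = 0.306.

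| g (points, assumed) | Bias (points) | Bias / SE | False-positive rate |
|---|---|---|---|
| 0 (equally atypical) | 0 | 0 | 5% |
| 1 | 0.1 | 0.33 | 6.2% |
| 2 | 0.2 | 0.65 | 9.9% |
| 3 | 0.3 | 0.98 | 16.3% |

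The sign can go either way. A gap of 3 points is 2 SD and stands at the severe end.

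**4. What the earlier visits could add in power** (normal approximation, δ = 1.0). Suppose every lost patient has an earlier VAS that correlates ρ with month 12. Effective n per arm = 47.7 / (1 − 0.10 × ρ²).

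- Observed cases only: 47.7 per arm, power 90.2%. With the Mann–Whitney efficiency of 3/π under normality, power is 88.9%.
- ρ = 0.5: 47.7 / 0.975 = 48.9, power 90.9%.
- ρ = 0.8: 47.7 / 0.936 = 51.0, power 92.0%.

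The gain over observed cases is 0.7 to 1.8 percentage points.

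**5. What the earlier visits could remove in bias.** Take g = 3. If the gap was already present at the earlier visit and ρ = 0.5 with equal SDs, the model predicts 0.5 × 3 = 1.5 points of it, and 0.10 × 1.5 = 0.15 remains. If nothing showed before loss, the full 0.3 remains. A mixed model therefore removes only the part that earlier VAS predicts.

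**The case against.** **Exclusion is inferred.** A reader might conclude that the plan drops the lost 10% and runs a completers analysis under a false label. The article does not say so. A Mann–Whitney test can be run on imputed values, and the missing-data rule may stand in the full protocol or analysis plan, neither of which is shown. Silence on that rule is not itself a fault. This objection stands. What remains is that the one method the article names cannot deliver its stated principle without such a rule.

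**Differential loss is not documented.** A reader might also infer that loss will favour the prosthesis, because the Discussion names dislocation and loosening as its most common complications. Those are adverse events and do not amount to missing data. Such patients stay in their arm under intention-to-treat and may be seen more often. Adverse events are followed up, and patients who miss a visit are phoned with a new appointment. This stands too: neither direction nor size can be claimed.

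**The earlier VAS values are not certain, and not everyone can be retained.** VAS at 6 weeks, 3 and 6 months is implied only. Patients lost before 6 weeks have no post-operative VAS, and use of withdrawn patients' data depends on their agreement (Follow-up and outcomes measures). All of this stands and limits what the fix can achieve.

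**The change is partly a preference.** Replacing a rank test with a parametric model brings in assumptions that the plan avoided. This is met in part by keeping the rank test as a supportive analysis. The proposed model also uses baseline VAS, the stratification factors and visits already scheduled, all of which the named analysis leaves out.

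**Conclusion.** The concern holds in limited form. Unless values are imputed, the named primary test uses about 95 of 106 randomised patients and does not by itself carry out the intention-to-treat principle attached to it. Power is not the issue, because the sample size already allows for the loss. The exposure is to bias of unknown direction: none if lost patients are equally atypical in both arms, and 0.1 to 0.3 points for gaps of 1 to 3 points, with false-positive rates of about 6% to 16%.

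These figures rest on 10% loss in each arm, SD 1.5 and 48 observed per arm. The 48 and the 1.0-point difference are solved backwards, and the gaps are illustrative. The change is worth making because a concrete alternative can use data already scheduled. The documents do not show that the planned result would be biased.

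**What to change.** Name as the primary analysis a mixed model for repeated measures on VAS at the scheduled post-operative visits up to 12 months: 6 weeks, 3 and 6 months if VAS is recorded there, and 12 months. Include treatment by visit, baseline VAS, sex and age group. Make the 12-month treatment contrast primary, and analyse patients in their assigned arm.

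Add one delta-adjusted sensitivity analysis for patients missing at 12 months, with the shift allowed to differ between arms. Keep the Mann–Whitney test as a supportive observed-case analysis, and do not describe it as including all randomised patients. Confirm in the text that VAS is collected at the earlier visits.

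The cost is a change of analysis wording and modest programming, which the named software can handle. No extra patients or visits are needed. The article gives the trial as still recruiting, with recruitment expected to end in February 2026, so the change should be fixed before any 1-year comparison by arm is made. The model relies on missing-at-random and on parametric assumptions. It cannot recover patients with no post-operative VAS or those who refuse use of their data, and it adds at most about 2 points of power.

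### The primary test is fixed as an unadjusted Mann–Whitney U and labelled a mean comparison; an ANCOVA on variables already collected would be more precise and would return a mean difference

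*Protocol article*

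**What the plan says.** Under Primary analysis at 1 year, the article states that the main variable, VAS, "will be used as a continuous variable to confirm the main hypothesis, and a non-parametric mean comparison analysis" will be carried out, and names it as the Mann–Whitney U test, by intention to treat. No covariate is mentioned. For the other outcomes, the same section allows Student's t or Mann–Whitney "test for the resultant variables".

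Four other places bear on this:

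- The abstract says "The trial’s primary outcome variable is the change in the visual analog scale (VAS) from baseline to 12 months". Follow-up and outcomes measures agrees in substance: "The primary outcome measure will be the visual analog scale (VAS) determined by changes in the distance between the patient-made marks". The analysis section says only VAS.
- Sample size sets the trial up "to detect differences equal to or greater than 30% in the visual analog scale (VAS) on the baseline status of the patient", two-sided alpha 0.05, beta 0.1, with 10% loss. It adds: "The common standard deviation is assumed to be 1.5".
- Randomization and blinding says: "Randomization will be stratified by sex and group age".
- Data collection method and management makes baseline measurement a condition of surgery, so baseline VAS should be complete in operated patients.

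**The concern.** Mann–Whitney addresses whether a patient in one arm tends to rank above a patient in the other. That is not a comparison of means, so the label misdescribes the test. The sample size uses the inputs of a two-mean comparison, and the health economics section needs a mean difference in effect for its cost-effectiveness ratio. The primary test as named supplies neither.

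The second issue is precision. The trial will hold baseline VAS for every operated patient, and it stratifies on sex and age group. The named test uses baseline only through subtraction, if the change is what is tested, and does not use the strata. Subtraction removes the whole baseline value whatever its correlation with the outcome, whereas a regression adjustment removes only the part that predicts it. A single centre expecting to recruit for five to six years should not give up that precision when recovering it costs nothing.

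**Working it through.** **Inputs from the article.** SD 1.5; two-sided alpha 0.05; power 90%; 53 per arm, 106 in total; 10% loss. **Not in the article:** the absolute difference, whether 1.5 is the SD of the change or of the 12-month score, and the correlation ρ between baseline and 12-month VAS. The last two are handled as ranges.

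**Step 1: the plan's own figure.** For two means, n per arm = 2·SD²·(1.960 + 1.2816)²/δ². With SD 1.5 and δ = 1.0 this is 2 × 2.25 × 10.507 = 47.28, so 48. Adding 10% gives 48 × 1.1 = 52.8, so 53 per arm and 106 in total, the stated figure. Dividing by 0.9 instead gives 54 per arm and 108. With δ = 0.95 the total is 118, and with δ = 1.05 it is 96. The stated size therefore fits a difference of about 1.0 point, which as 30% of baseline implies a baseline VAS of 1.0/0.30 = 3.3. The 1.0 is inferred, not stated.

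**Step 2: cost of ranks alone.** Power = Φ(δ/(SD·√(2/n)) − 1.960).

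- Mean comparison, n = 48: 1/(1.5 × 0.2041) = 3.266; Φ(1.306) = 90.4%.
- Mann–Whitney, normal data, relative efficiency 3/π, effective n = 45.8: Φ(1.232) = 89.1%.

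The loss is about 1.3 points. A simulation of 20,000 trials gave 90.1% for the t-test and 88.8% for Mann–Whitney.

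**Step 3: baseline adjustment.** With equal variance s² at both times, Var(change) = 2s²(1 − ρ) and the ANCOVA residual variance is s²(1 − ρ²), a ratio of (1 + ρ)/2.

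- If 1.5 is the SD of the change, the ANCOVA SD is 1.5·√((1 + ρ)/2): 1.209, 1.299 and 1.383 at ρ = 0.3, 0.5 and 0.7.
- If 1.5 is the SD of the 12-month score, the ANCOVA SD is 1.5·√(1 − ρ²): 1.431, 1.299 and 1.071. The SD of the change is 1.5·√(2(1 − ρ)): 1.775, 1.500 and 1.162.

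Power at δ = 1.0 and 48 per arm:

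| ρ (assumed) | Mann–Whitney on change, 1.5 = SD of change | ANCOVA, 1.5 = SD of change | Mann–Whitney on change, 1.5 = SD of 12-month score | ANCOVA, 1.5 = SD of 12-month score |
|---|---|---|---|---|
| 0.3 | 89.1% | 98.2% | 77.0% | 92.8% |
| 0.5 | 89.1% | 96.5% | 89.1% | 96.5% |
| 0.7 | 89.1% | 94.3% | 98.5% | 99.6% |

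If 1.5 is the SD of the 12-month score and Mann–Whitney is applied to that score rather than to the change, its power is 89.1% at every ρ, still below the last column.

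**Step 4: where the gain comes from.** At ρ = 0.5, replacing ranks by means moves power from 89.1% to 90.4% (1.3 points), and adding baseline as a covariate moves it to 96.5% (6.1 points).

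**Step 5: in patients.** For 90% power, Mann–Whitney needs 47.28 × π/3 = 49.5, so 50 evaluable per arm. ANCOVA needs 31, 36 or 41 (SD of change) or 44, 36 or 25 (SD of 12-month score) at ρ = 0.3, 0.5 or 0.7.

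These figures leave out any further gain from adjusting for sex and age group.

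**The case against.** The best defence is that a prespecified Mann–Whitney test on the change score, in a 1:1 randomised trial, is a valid test of the null hypothesis that the arms have the same distribution. Randomisation guards against systematic imbalance, and leaving out stratification factors usually makes a test somewhat conservative rather than misleading. A Hodges–Lehmann shift with an interval could accompany it, and how estimates are presented is commonly left to a full protocol or analysis plan not shown here. All of this stands, so the absence of a stated estimate or interval is not counted as an omission. The defence does not cover the label or the choice of an unadjusted test, both of which the article states itself. A Hodges–Lehmann shift is also not a mean difference in general.

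Four stronger readings are tempting, and the document does not support them:

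- **That baseline VAS is ignored.** The outcome is defined as a change, so baseline enters by subtraction. What is missing is its use as a covariate.
- **That the trial states a 1.0-point target.** It states 30% relative to an unstated baseline; 1.0 is only what fits 106.
- **That the primary test depends on observed normality.** It is fixed as Mann–Whitney. The choice between two tests concerns other outcomes, and the article gives no explicit rule for it.
- **That ranks would favour the implant because a minority of failures is underweighted.** The Discussion cites 5 failures among 80 patients and 18 revisions among 156, from other series. It gives no timing for those counts and does not say that these patients had no pain relief at 12 months. Such an argument would also compare arms with different distributions, so a rejection would not be a false positive of the test.

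**Conclusion.** The point holds as a should-fix. The mislabelling and the mismatch with the SD-based sample size are plain from the text and need no assumption. The loss of precision is real, but its size depends on assumptions: a back-solved difference of about 1.0 point, 48 evaluable per arm, normal data, equal variance at baseline and 12 months, and ρ between 0.3 and 0.7, which the article does not give. On these, ANCOVA has more power than the planned test under both readings of the SD: 94–98% against 89%, or 93–99.6% against 77–98.5%. The advantage over Mann–Whitney on the change is large when ρ is low (15.8 points at ρ = 0.3 if 1.5 is the SD of the 12-month score) and small when ρ is high (1.1 points at ρ = 0.7 on the same reading). Most of it comes from the baseline covariate rather than from leaving ranks.

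**What to change.** Make the primary analysis an ANCOVA of 12-month VAS on treatment arm, baseline VAS, sex and age group, reporting the adjusted mean difference with 95% CI and p-value. Keep Mann–Whitney on the change from baseline as a sensitivity analysis, described as a comparison of rank distributions. Use the same model, with each outcome's own baseline, for QuickDASH, PRWE, strength and range of motion. In Sample size, state the absolute difference targeted and whether 1.5 is the SD of the change or of the 12-month score.

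The cost is a wording change to the analysis section. It needs no new data, and ANCOVA is a standard procedure in the named software. Trial status describes the trial as still recruiting, so the change can be made and dated before any comparative results are seen.
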